### 5.5.2. Blinding method

[figure not shown]

The imaging data will be anonymized, by a person who will not be part of the image reviewers, to remove all information related to the patient's identity from the DICOM fields of the image (metadata). A number will be assigned to each patient, using a randomization table. The patient's identity - anonymization number correspondence will be collected in a specific database.

Images will be read at the end of the inclusions, from the anonymized data, by two senior doctors, on a post-processing console. The anonymization method will not identify the patient's identity or the type of device used (LEHR or LEHRS collimator).

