| CRITERIA FOR NON-INCLUSION OF SUBJECTS | Children, pregnant women or women at risk of pregnancy, Patients under guardianship or under trusteeship, known renal failure, patients with pain, patients who cannot have a standard good quality scintigraphic examination.                                                                                                                                                    |
| STRATEGIES / PROCEDURES                | The patient's scans will be performed on 2 separate devices and the images obtained will be compared.                                                                                                                                                                                                                                                                             |
| NUMBER OF PATIENTS                     | 85 patients including 70 for bone scans                                                                                                                                                                                                                                                                                                                                           |
| DURATION OF THE SEARCH                 | Duration of the inclusion period: 1 year

Duration of participation for each patient: less than half a day.

Total duration of the study: 12 months (data inclusion and analysis)                                                                                                                                                                                     |
| EXPECTED BENEFITS                      | As individual for the patient: likely to improve the image quality of his examination, interpretation of the examination by 2 expert doctors.

Collectively: improvement of image quality of scintigraphic exams with this collimator allowing to reduce the duration of exam and/or the injected activity of radiopharmaceutical drugs (improvement of patient dosimetry). |

[figure not shown]

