### 5.1. RESEARCH METHODOLOGY

Monocentric, comparative, non-inferiority study, with intra-patient comparisons (acquisition vs LEHR Siemens reference collimator, for each patient).

Interpretation of image quality in double-blind mode.

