### **9.3. CONFIDENTIALITY OF DATA**

In accordance with the provisions concerning the confidentiality of data to which persons responsible for quality control of biomedical research have access (Article L. 1121-3 of the Public Health Code), in accordance with the provisions relating to the confidentiality of information concerning in particular the nature of the products, the tests, the persons who lend themselves to them and the results obtained (Article R. 5121-13 of the Public Health Code), persons having direct access shall take all necessary precautions to ensure the confidentiality of information relating to the products, the tests,

[figure not shown]

the persons who lend themselves to them and in particular with regard to their identity and the results obtained.

These persons, like the investigators themselves, are subject to professional secrecy (under the conditions defined by Articles 226-13 and 226-14 of the Criminal Code).

During or at the end of biomedical research, data collected on suitable individuals and transmitted to the sponsor by investigators (or any other specialized stakeholders) will be made anonymous.

Under no circumstances should they disclose in plain language the names of the persons concerned or their addresses.

Only the first letter of the subject's name and the first letter of the subject's first name will be registered, accompanied by a study-specific coded number indicating the order in which the subjects are included. Patient images will be anonymized, using a specific feature of the image processing console.

The sponsor shall ensure that each person who is suitable for the research has given his or her written consent to access the individual data concerning him or her that are strictly necessary for the quality control of the research.

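### Section 5.5.2 promises device masking but codes images by patient, so a patient's two image sets stay linked when they are scored

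*Protocol*

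**What the plan says.** Section 5.1 describes a single-centre, non-inferiority, within-patient comparison and specifies "Interpretation of image quality in double-blind mode". The Executive Summary gives the imaging plan: "The patient's scans will be performed on 2 separate devices and the images obtained will be compared".

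Section 5.5.2 sets out the blinding in four elements:

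- **De-identification.** It is done "by a person who will not be part of the image reviewers", whose task is "to remove all information related to the patient's identity from the DICOM fields of the image (metadata").
- **Coding.** "A number will be assigned to each patient, using a randomization table". A separate database holds the link between patient identity and number.
- **Reading.** "Images will be read at the end of the inclusions, from the anonymized data, by two senior doctors, on a post-processing console".
- **Result claimed.** "The anonymization method will not identify the patient's identity or the type of device used (LEHR or LEHRS collimator").

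Section 9.3 adds one detail on the tool: "Patient images will be anonymized, using a specific feature of the image processing console". It does not list the fields that this feature covers.

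Section 3.3 asks for a separate 1 to 5 score for each patient, collimator and image type. The main comparison is the share of examinations scoring 4 or 5.

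**The concern.** The unit that is scored is the image set: one patient, one collimator, one image type. The unit that is coded is the patient. A code at patient level hides who the patient is, but it does nothing to hide which sets belong together.

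A reader who knows that two sets are a pair can score the second with the first in mind. The primary criterion turns on a subjective cut between 3 and 4, where the scale separates moderate from low background noise and blurred from good visualization. Small adjustments at that cut change the endpoint. Seeing the pair also makes a consistent difference in appearance between the two cameras easier to notice than it would be from single images in shuffled order. That is how linkage could erode the device masking that section 5.5.2 promises.

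Masked reading carries much of the protection against bias here. Section 5.5.1 rules out a random draw, and which camera comes first depends on the appointment slot.

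**Working it through.** No formula or stated figure is at issue, so the check compares the property claimed with the steps that would produce it.

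**1. Units.** Section 2.2 gives every bone-scan patient a late whole-body scan in the standard examination and a second one for the study. The Executive Summary plans 85 patients, 70 of them for bone scans.

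- Whole-body sets in the primary population: 70 × 2 = 140, under 70 numbers.
- All patients, at one set per camera: 85 × 2 = 170 sets, under 85 numbers.
- Static images, and tomoscintigraphy where performed, add further sets under the same numbers.

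**2. What the randomization table does.** It allocates numbers to patients, so it can scramble the order of patients. It does not act within a patient, which is where the two cameras are compared.

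**3. What the stated key does.** The database links identity to number, also at patient level. Yet each score must be traced to a collimator for the analysis. A patient number alone cannot do that, so some further label or order must distinguish the two sets. The protocol does not say what it is or whether readers see it. If it were constant across patients, recognising it once would carry over to the rest.

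**4. What the metadata step does.** The operation described concerns patient identity. Manufacturer, model, station and acquisition fields are not patient identity, so this wording does not reach them. The closing sentence of section 5.5.2 covers device type as a result, without naming the step that achieves it.

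**5. What is said about presentation.** Reading takes place after inclusions end, on a post-processing console, by two doctors. The section does not say whether a patient's two sets are shown together, in what order, or in how many sessions.

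**6. Direction of any bias.** If linked reading pulls the two scores together, it shrinks the observed difference and favours a non-inferiority conclusion. If direct comparison sharpens contrasts, it does the opposite. If a reader recognises a camera, scores could move either way. The protocol has no data on any of these, so neither sign nor size can be given.

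**The case against.** A reader might infer that only patient identity is removed, that readers can therefore tell the vendor, and that the double-blind label is wrong. The protocol does not support this. Section 5.5.2 makes non-identification of the device a stated property of the method. Nothing says that manufacturer or model fields are left in place; the text does not list them either way. The console feature in section 9.3 may strip them, and a figure under the blinding heading, not visible in the text examined, may show more. Recognising a pair does not by itself reveal which camera produced which set.

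Other points on that side:

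- **Dependence is part of the design.** Two images of one patient are correlated, and section 8 names a paired signed-rank test. This is right. The concern is the additional dependence that arises when the reader lets one score influence the other; a paired test does not remove a bias from that source.
- **Safeguards exist.** A non-reader anonymises, reading is deferred, two doctors read, and kappa is planned. The first two protect patient identity and reduce recall of cases. Kappa measures agreement between readers and would not reveal an influence that both share because both see linked pairs.
- **Reading logistics may sit in a manual.** A list of DICOM tags can reasonably be left there. The coding unit cannot be treated the same way, because section 5.5.2 fixes it, at patient level.

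What stands of the objection is that unblinding is not shown and that side-by-side reading is a possibility left open, not a stated practice.

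**Conclusion.** The point holds in a limited form. Section 5.5.2 assigns one number per patient in a design with two image sets per patient to be compared, and describes nothing that separates or shuffles those sets. As written, the pair is linked at scoring, so the scores may not be independent and device masking may be weaker than claimed. Removing device identifiers belongs in the same correction, because the masking is asserted as a result while the operation described covers patient identity.

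The conclusion assumes that the patient number is the code the readers see; the section describes no other. Bias is possible, but its direction and size cannot be estimated from the protocol. This is an inexpensive improvement to make before reading starts, not a demonstrated failure of blinding, and it gives no reason to withdraw the double-blind description. Confidence is medium.

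**What to change.** Amend section 5.5.2 so that the non-reader already assigned to anonymise:

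1. gives each image set (patient by collimator by image type) its own random code, in place of one number per patient on the images;
2. records the link from code to patient, collimator and image type in the existing correspondence database, closed to the readers until scoring is complete;
3. removes device-identifying fields and burnt-in labels in the same pass, so that the stated device masking is produced by a described step;
4. presents the sets to each reader in random order, with a patient's two sets in separate sessions.

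The cost is a longer coding list (at least 140 whole-body codes for the bone scans instead of 70 patient numbers) and reading split into sessions. No extra patient, scan or reader is needed.

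The change should stop short of resampling both cameras' images to one matrix and pixel size. That could alter the resolution and noise that the section 3.3 scale is meant to grade.

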## **5.6. DATA COLLECTED IN THE OBSERVATION BOOKLET**

- Patient data: age, sex, weight, BMI.
- Radiopharmaceutical drug-related data: radiopharmaceutical drug name, injected activity, time and injection site.
- Data related to acquisitions: acquisition times, physical parameters (peak energy, fenestration, acquisition time, time per projection and number of projections if tomoscintigraphy...)

As with the standard review, the study imaging data will be stored and archived in the institution's PACS.

## **5.7. DESCRIPTION OF THE RULES FOR PERMANENT OR TEMPORARY CESSATION**

### **5.7.1. Stopping a person's participation in research**

Subjects may withdraw their consent and ask to leave the study at any time and for any reason. In the event of early discharge, the investigator should document the reasons as fully as possible.

The investigator may temporarily or permanently suspend the participation of a subject in the study for any reason that would best serve the interests of the subject, particularly in the event of painful symptomatology or major claustrophobia during acquisitions.

A patient's discharge from a study will not change his or her usual management of the disease.

### **5.7.2. Stop some or all of the research**

The study may be stopped prematurely if unexpected, serious adverse events occur that require a review of the strategy profile. Similarly, unexpected events or new product information, in the light of which the objectives of the study or clinical program are unlikely to be achieved, may lead the sponsor to prematurely discontinue the study.

[figure not shown]

The ORLEANS CHR reserves the right to discontinue the study at any time if it appears that the inclusion objectives have not been met.

## **6. PRODUCTS ADMINISTERED TO RESEARCH SUBJECTS**

---

An injection of radiopharmaceutical drug, necessary for the standard scintigraphic examination, will be carried out, as in current practice. There will be no additional injection related to the research protocol. The summaries of product characteristics (RCP) of the radiopharmaceuticals used in this study are presented in the Appendix.

### **6.1. AUTHORIZED TREATMENTS**

Usual treatment of the patient, analgesics....

### **6.2. UNAUTHORIZED PROCESSING**

No processing is involved. Any treatment not authorized for the standard examination will result in its cancellation and, in fact, participation in the study (verification of the latest chemotherapy dates, injection of biphosphonates, synthetic antithyroid agents and thyroid hormones...)

### **6.3. EMERGENCY TREATMENT**

Not concerned. No major adverse reactions are documented for radiopharmaceuticals used in the standard review.

## **7. SECURITY ASSESSMENT**

---

### **7.1. PROCEDURES IN PLACE FOR RECORDING AND REPORTING ADVERSE EVENTS**

As this is a category 2 study, no particular vigilance related to the research protocol will be required.

However, the monitoring and reporting of incidents and incident risks resulting from participation in the study will be reported through usual channels. As the collimator and the software used are CE marked, any adverse events will be the subject of a material report by ORLEANS CHR.

## **7.2. SUPERVISORY COMMITTEE**

Since participation in the study did not pose any risk to the patient, it was not considered necessary to set up a monitoring committee.

## **7.3. METHODS AND DURATION OF FOLLOW-UP OF INDIVIDUALS FOLLOWING THE OCCURRENCE OF ADVERSE EVENTSS**

Each adverse event will be monitored until it is fully resolved (stabilized to a level acceptable to the investigator or returned to its previous state) even if the patient has been discharged from the trial.

# **8. STATISTICS**

---

For statistical analysis, data were collected on Excel spread sheet and analyzed using the Statistical Package for Social Sciences (SPSS; IBM SPSS, Armonk, NY, USA).

Sample size was calculated with expected performances on phantom.

For hypothesis testing, a non-parametric Wilcoxon signed rank test was used for categorical and non-Gaussian distribution variables (variable's distribution was tested with a Kolmogorov-Smirnov normality test).

A non-inferiority test was also performed.

Inter-observer agreement was assessed with a Cohen's kappa test. The level of agreement was classified into six Landis and Koch categories

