| MAIN OBJECTIVE              | Compare image quality obtained with the new LEHRS GE collimator versus a standard Siemens LEHR collimator in bone scan studies.                                                                                                                                                                                                                                                                                                                                                              |
| SECONDARY OBJECTIVES        | Evaluation of image quality in pulmonary, thyroid, parathyroid and brain scans with DaTSCAN.

Performances evaluation on physical measurement phantoms.                                                                                                                                                                                                                                                                                                                                |
| MAIN JUDGMENT CRITERION     | Rate of images obtaining a score greater than or equal to 4 on visual image quality analysis (on a 5-point LIKERT scale).                                                                                                                                                                                                                                                                                                                                                                    |
| SECONDARY JUDGMENT CRITERIA | Signal-to-noise ratio measurements on patient acquisitions.

Physical performances of the new LEHRS collimator using physical measurement phantoms.                                                                                                                                                                                                                                                                                                                                    |

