## **2.3. SUMMARY OF RESULTS OF AVAILABLE NON-CLINICAL AND CLINICAL TRIALS**

No study has yet been realized to evaluate this new collimator.

Few data from the literature are available on the evaluation of new collimators in nuclear medicine. Most studies are medical physics studies with evaluation of performances in terms of sensitivity and resolution on physical measurement objects (e.g., evaluation of a new collimator in mammary tomosynthesis, Gilland et al. Med Phys 2017 Nov;44(11):5740-5748). An evaluation of the old and new collimator on physical measurement objects is planned in our study.

Our research work can be compared to the studies realized after the commercialization of solid-state nuclear medicine cameras (known as CZT, for cadmium-zinc-telluride). For example, in the retrospective study conducted by the CCN team (Songy et al, Clin Nucl Med. 2011 Sep;36(9): 776-80), 153 patients received their cardiac scans on an older generation camera and then on the new CZT camera. The data were analyzed retrospectively, comparing image quality and also the final diagnosis.

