### **3.3. MAIN EVALUATION CRITERIA**

The main evaluation criterion will be the image quality evaluation on bone scanning obtained with the new LEHRS GE collimator vs. standard Siemens LEHR collimator (two expert nuclear physicians).

There is no standard criteria for evaluating image quality in scintigraphy. A good quality scintigraphic image (sensitive and good spatial resolution) will present good bone fixation, with low background noise, well defined bone surfaces, and good visualization of interosseous spaces.

We will therefore use a 5-point Likert scale :

- 5 Diagnostic quality - Excellent image quality and resolution (excellent bone fixation, almost non-existent background noise, good visualization of bone surfaces and interosseous spaces)
- 4 Diagnostic quality - Good image quality and resolution (good bone fixation, low background noise, good visualization of bone surfaces and interosseous spaces)
- 3 Diagnostic quality - Acceptable image quality and resolution (good bone fixation, moderate background noise, blurred visualization of bone surfaces and interosseous spaces)
- 2 Suboptimal quality - Limited clinical information (poor bone fixation, moderate to high background noise, poor visualization of bone surfaces and interosseous spaces)
- 1 Non-diagnostic quality (poor bone fixation or almost no bone fixation, high background noise)

For each patient, this score will be established for each image type and for each collimator, e.g. whole body scanning, static imaging, tomoscintigraphy (if performed).

The percentage of examinations judged to be of good quality (scores 4 and 5) will be compared for each collimator and each image type.

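### A declared paired non-inferiority study fixes no margin or decision rule, names a difference test for hypothesis testing, and does not tie its 70 bone-scan patients to the primary endpoint

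*Protocol*

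**What the plan says.** - **Design.** Section 5.1 describes the study as "Monocentric, comparative, non-inferiority study, with intra-patient comparisons". The Executive Summary gives the same design.
- **Main criterion.** The Executive Summary defines it as "Rate of images obtaining a score greater than or equal to 4 on visual image quality analysis", on a 5-point Likert scale. Section 3.3 adds: "The percentage of examinations judged to be of good quality (scores 4 and 5) will be compared for each collimator and each image type". The outcome is therefore binary and paired within patient.
- **Named test.** Section 8: "For hypothesis testing, a non-parametric Wilcoxon signed rank test was used for categorical and non-Gaussian distribution variables".
- **Non-inferiority test.** Section 8, in full: "A non-inferiority test was also performed". No margin, significance level, interval or decision rule appears there or elsewhere in the protocol.
- **Size.** The Executive Summary gives "85 patients including 70 for bone scans". The only basis, in section 8, is: "Sample size was calculated with expected performances on phantom".
- **Prior evidence.** Section 2.3: "No study has yet been realized to evaluate this new collimator". The same section describes phantom work as measuring sensitivity and resolution on physical objects.

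**The concern.** A non-inferiority hypothesis is defined by its margin. Until the margin is fixed, there is no null hypothesis to reject and no error rate to control. The one test that section 8 names for hypothesis testing has a null of no difference and contains no margin. Applied to the binary criterion it reduces to a McNemar or sign test. Applied to the 5-point score it addresses something other than the declared rate. In neither case is a non-significant result evidence that the new collimator is acceptably close to the reference.

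The sample size has a related gap. A paired non-inferiority size needs the expected rates, or at least the proportion of patients whose two images fall on opposite sides of the cut at 4, together with a margin. Sensitivity and resolution on a phantom provide none of these.

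The study's main claim is at stake. A reader of the results could not tell whether the margin came before or after the scores, nor what 70 patients were meant to rule out.

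**Working it through.** **1. Can the 70 be reproduced?** No. The protocol gives no margin, significance level, power, expected rate or discordance, so everything below rests on assumed values.

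For a paired binary outcome with true difference 0, discordance ψ and margin δ:

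n = (z(1−α) + z(power))² × ψ / δ²

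With one-sided α = 2.5% and 80% power, (1.960 + 0.842)² ≈ 7.849. For example, ψ = 0.20 and δ = 0.15 give 7.849 × 0.20 / 0.0225 = 69.8, so 70 pairs.

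| Discordance | Pairs, δ = 5 points | δ = 10 points | δ = 15 points |
|---|---|---|---|
| 10% | 314 | 79 | 35 |
| 20% | 628 | 157 | 70 |
| 30% | 942 | 236 | 105 |

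A search over one-sided α of 2.5% or 5%, power of 80 to 90%, discordance of 5 to 50% and margins of 5 to 20 points found 19 combinations with n within 2 of 70. Their margins run from 8 to 20 points. The number 70 therefore implies no particular margin.

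**2. What do 70 pairs deliver?** (One-sided 2.5%, true difference 0.)

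Margin reached with 80% power = 2.802 × √(ψ/70). Power at a 10-point margin = Φ(0.10/√(ψ/70) − 1.960).

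| Discordance | √(ψ/70) | Margin at 80% power | Power, δ = 10 points |
|---|---|---|---|
| 10% | 0.0378 | 10.6 points | Φ(0.686) = 75% |
| 20% | 0.0535 | 15.0 points | Φ(−0.089) = 46% |
| 30% | 0.0655 | 18.3 points | Φ(−0.433) = 33% |

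**3. Could the difference test stand in?** Suppose LEHRS is truly 10 points worse and 70 pairs are tested at two-sided 5%. The chance of a non-significant result is found by enumerating the discordant counts. Let b be the pairs favouring LEHR, with probability (ψ + 0.10)/2, and c the pairs favouring LEHRS, with probability (ψ − 0.10)/2. The normal-approximation test uses |b − c|/√(b + c) against 1.96. The exact test is the binomial sign test.

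| Discordance | Non-significant, normal approximation | Non-significant, exact |
|---|---|---|
| 10% | 7% | 29% |
| 20% | 54% | 63% |
| 30% | 66% | 74% |

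The 10% row is a boundary case: a 10-point deficit with 10% discordance means that every discordant pair favours LEHR (c = 0). A cross-check with standard error √((ψ − 0.10²)/70) gives 52% at 20% discordance and 66% at 30%, in line with the enumeration.

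**The case against.** Several points can fairly be made for the protocol.

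- **A non-inferiority test is planned.** It is unspecified rather than absent, and the word *also* does not prove that it ranks below the Wilcoxon test. This stands. A reader might infer that the study cannot yield a valid non-inferiority conclusion at all, but the text supports only that section 8, as written, does not secure one.
- **The Wilcoxon test is assigned generically** to categorical and non-Gaussian variables. It suits the 5-point score and could serve the signal-to-noise ratios. This stands: the test is not wrong in itself. It cannot answer the question that the design asks.
- **Nothing says that a non-significant result will be read as equivalence, or that the margin will be set after the data.** This also stands. Both are risks that the text leaves open, not stated intentions. Section 5.5.2 has the images read only after inclusions end, so a margin could still be fixed in time.
- **Sizing on expected phantom performance does not conflict with phantom work still being planned.** Correct: expected values are not measured ones, and there is no circularity. What remains is that phantom quantities do not translate into a rate of Likert scores.
- **Detail may sit in a separate analysis plan,** which is not at hand. That would cover the interval method and any superiority step. It would not excuse the protocol from giving a margin and a sample size tied to the endpoint.

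**Conclusion.** The concern holds in this form: the protocol declares non-inferiority on a paired rate, fixes no margin or decision rule, names only a difference test for hypothesis testing, and gives 70 no stated link to the primary endpoint.

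A reader might conclude that 70 patients are too few. The documents do not support that. At 20% discordance, 70 pairs would give about 80% power for a 15-point margin. The number can be neither confirmed nor refuted because nothing it depends on is stated.

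All power, margin and non-significance figures rest on assumed discordance, significance level and true difference. How often a difference test would miss a 10-point deficit depends heavily on discordance, from 7% (29% exact) at the 10% boundary to 66% (74% exact) at 30%. The absence of a margin depends on none of these assumptions. It should be corrected before the images are read.

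**What to change.** In section 8, before any image is read:

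1. **Primary analysis.** State the paired difference, LEHRS minus LEHR, in the proportion of bone-scan examinations scored 4 or more. Name one primary image type that all bone-scan patients have, for example whole body. Section 2.2 provides tomoscintigraphy only in some cases, so 70 pairs would not be available for it. State how the two readers' scores are combined.
2. **Decision rule.** Use a two-sided 95% paired interval, such as Tango's score interval or the paired Newcombe interval. Declare non-inferiority only if the lower limit lies above −δ.
3. **Margin.** Write δ down and justify it by the loss of image quality that would be acceptable. Do not derive it from what 70 pairs can support.
4. **Wilcoxon test.** Keep it on the 5-point score as a supporting analysis, and say that it cannot establish non-inferiority.
5. **Sample size.** Leave the phantom rationale on record as history. Add the power or precision that 70 pairs give for the chosen δ over a range of assumed discordance.

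The cost is a rewritten paragraph and a decision on margin, image type and reader rule. No extra patients or data are needed. The stated power may look less favourable than readers now suppose.
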